### Phase-II randomized controlled trial protocol

#### Methods and design

This study will be a two-armed blind RCT that will recruit children referred for dental extractions under general anaesthesia, as well as their parents. The participants will be randomized into two groups. In the study group, the child and escort will undergo self-directed ‘play’ about oral health using the video game on an iPad and receive a copy on a DVD to run it on a home personal computer. In the control group, the child and escort will receive verbal oral health advice from a dental nurse who has a health promotion qualification.

The participants will be recruited at the medical pre-assessment clinic at the day surgery unit at King’s College Hospital in London. All children scheduled for a procedure under general anaesthesia attend this clinic approximately two weeks prior to their surgery for a medical evaluation of fitness to undergo general anaesthesia.

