#### Sample size

The primary outcome measure in this study is user satisfaction with the intervention, assessed using a visual analogue scale. This is constructed as a continuous 100 mm line, with a score at the 0 mm mark indicating complete dissatisfaction with the intervention and a score at the 100 mm indicating complete satisfaction. As far as we know, this is the first study measuring patient’s satisfaction with the use of video games for oral health education. Assuming that our population will have a standard deviation of 25 mm, which is similar to patient satisfaction measured in studies in other fields [29], and aiming to detect a difference of at least 15 mm between the groups to indicate its clinical significance, a sample of 45 participants in each group will be needed to provide 80 % power, at the 5 % significance level, to detect effects of size 0.6 and above. This number of participants is also sufficient based on our calculations using the results of the pictorial dietary quiz used in the phase-I RCT. Anticipating a 20 % dropout rate [30], we intend to recruit approximately 108 participants.

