#### Randomization and blinding

A computer-generated simple randomization grid will allocate the participants to the two groups. The randomization process will be overseen by the unblinded researcher (MTH). The allocation of participants will be performed by the two trained dental nurses responsible for applying the interventions to the participants. The researcher (AA) will remain blinded all through data collection and input. The statistician will also be blinded during the analysis. Only after data collection is complete will one researcher (MTH) break the randomization code to input the group allocation within the pre-existing data set and enable between-group analyses. The statistician and lead researcher (AA) will remain blinded.

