After the baseline measures are completed, AA will introduce the participants to the dental nurse and leave, to ensure that he remains blinded to group allocation. The nurse will then allocate the participants to either the video-game group or the control group according to the randomization grid and will apply the intervention accordingly.

The nurse will administer postintervention measures to both groups including: (i) pictorial dietary quiz, completed by the child; (ii) child’s and parent’s satisfaction with intervention on a visual analogue scale; (iii) a booklet that contains a toothbrushing diary and a snack diary, to be returned on the day of the general anaesthesia procedure. The booklet given to children from the study group will also contain a page in which they can write five ‘secret words’ that have been inserted in the DVD version of the game. This will allow us to determine whether participants used the game DVD at home. Children from the control group will have a simple colouring page instead. Finally, (iv) the nurse will ask the parent and child if they have any feedback on the intervention; this feedback will be written down verbatim (qualitative data).

AA will go to the day surgery unit on the day of the child’s general anaesthesia procedure to collect the booklet. He will also call the participating parents three months after their child’s general anaesthesia procedure and offer them a review appointment at the paediatric dentistry department. Upon attending, the parents of both groups will be asked to complete the children’s dietary questionnaire again, to measure any changes in dietary practices at home. The child will be asked to retake the pictorial dietary quiz to assess long-term retention of dietary knowledge. Attendance rates from both groups will be noted.

Fig. 2 is a summary of the recruitment process and the measures collected.

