Providing oral health education directly to the child might be questioned, since it is assumed that parents are responsible for the families’ oral health practices. However, there is some evidence that children play a role in shaping their oral health practices from a young age; Roberts et al. [38] suggested that children aged seven and older possess some control over their dietary selections in what is commonly known as ‘pester power’. It is important to note that Roberts et al. did not include children younger than 7, but other authors have suggested that children as young as 4 years old have a ‘pester’ or ‘nag’ power over their family’s food shopping [39]. Moreover, Birch and Fisher [40] suggested that even though young children have an innate preference for sugary foods, their dietary preferences are influenced by social and cultural norms, advertising and modelling. Providing children with oral health education through a potentially interesting method, such as video games, might provide them with a positive media influence. In addition, parents are indeed going to be part of the intervention in this study, as they will be required to guide the child through the game. Moreover, parents might learn indirectly, as some evidence suggests that children can transmit knowledge to their parents [41].

Selecting the measures used in this study has been difficult; considering the population targeted. This population is notoriously poor in attending dental clinics regularly [42, 43]. With that in mind, the phase-II RCT is designed to engage families in a positive way about oral health whilst simplifying data collection and reducing the time needed to complete the assessments. Despite this, we anticipate that following participants up at three months might be difficult; hence, we will offer telephone follow-up as an alternative.

The visual analogue scale is a low-burden measure that can be completed quickly and has been validated for use in measuring participant’s satisfaction [29, 30]. There is a risk that participants will feel inclined to give better scores for the nurse providing the control intervention. For this reason, qualitative data will also be collected. Nonetheless, it is recognized that parents might still give socially acceptable answers; thus, the interview approach is important, to ensure that participants feel comfortable in giving their responses.

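### The nurse who gives the control advice also administers the satisfaction scale that sets the sample size, and the stated safeguards do not protect that comparison

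*Protocol article*

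**What the plan says.** Four parts of the Protocol article bear on this.

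- **Powered outcome.** Sample size: "The primary outcome measure in this study is user satisfaction with the intervention, assessed using a visual analogue scale". Under Statistical analysis, the two arms' parent and child scores are compared by Student's t test.
- **Who knows the allocation.** Randomization and blinding: "The allocation of participants will be performed by the two trained dental nurses responsible for applying the interventions to the participants". The roles described there as blinded are the researcher and the statistician.
- **What is rated.** Under Methods and design, the control arm is personal contact: "the child and escort will receive verbal oral health advice from a dental nurse who has a health promotion qualification". The game arm is self-directed play on a tablet.
- **Who collects the rating.** Under Procedure for recruitment and application of intervention, the researcher leaves before allocation and "The nurse will then allocate the participants to either the video-game group or the control group according to the randomization grid". After the session, "The nurse will administer postintervention measures to both groups including: (i) pictorial dietary quiz, completed by the child", followed in the same list by "ii) child’s and parent’s satisfaction with intervention on a visual analogue scale" and by verbal feedback, which the nurse requests and writes down.

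The Discussion recognises the difficulty: "There is a risk that participants will feel inclined to give better scores for the nurse providing the control intervention". It offers two answers: collecting qualitative data, and an interview approach that puts families at ease.

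**The concern.** Satisfaction is a subjective score, and families cannot be blinded to whether they played a game or were given a talk. How the score is collected is therefore one of the few protections available. Here a control family hands its rating of a person's work to that same person. A game family hands its rating of a tablet to someone who did not personally deliver the content. Any courtesy is likely to be stronger in the first case, which is also the direction the protocol names.

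Acceptability is one of the trial's two research questions. A net courtesy effect towards control could hide a real preference for the game or produce an apparent preference for the nurse. Blinding data entry and analysis cannot undo it, because the score is already marked by then. A larger sample would not help either: the shift stays and is only estimated more precisely.

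**Working it through.** **Step 1. Do the stated safeguards reach the VAS?**

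| Safeguard | Who carries it out | Effect on the VAS comparison |
|---|---|---|
| Blinded researcher | Leaves before allocation | None at the moment of rating |
| Blinded statistician | Works on recorded scores | None at the moment of rating |
| Verbal feedback | The treating nurse | Open to the same courtesy; does not enter the t test |
| Comfortable interview approach | Not separated from the nurse | Concerns the manner of asking; the person rated still collects the rating |

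None of them separates the person being rated from the person collecting the rating.

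**Step 2. Reproduce the sample size.** Inputs from the Sample size section: difference 15 mm, SD 25 mm, 80% power, 5% level. Sidedness is not stated; two-sided is assumed.

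- Normal approximation: n per arm = 2 × (1.960 + 0.842)² × (25/15)² = 2 × 7.85 × 2.78 ≈ 43.6, so 44.
- Two-sample t test: 44.6, so 45. The stated 45 per group reproduces.
- Power at 45 per arm: 81.2% (normal), 80.4% (t).

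No stated figure is wrong because of this point; the question is bias.

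**Step 3. Effect of an assumed net shift.** Let b be the amount by which courtesy raises the control mean over and above any courtesy in the game arm. The documents give no value, so b from 0 to 10 mm is an assumption.

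- Standard error = 25 × √(2/45) = 5.27 mm.
- Power for a true 15 mm game advantage ≈ Φ((15 − b)/5.27 − 1.96).
- Rejection rate with no true difference = Φ(b/5.27 − 1.96) + Φ(−b/5.27 − 1.96).

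For b = 5: power ≈ Φ(1.897 − 1.96) = Φ(−0.063) = 47.5%. The rejection rate = Φ(−1.011) + Φ(−2.909) = 15.6% + 0.2% = 15.8%.

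| Assumed b (mm) | Power, true +15 mm for game: normal | Same: t test | Two-sided rejection, no true difference (normal) |
|---|---|---|---|
| 0 | 81.2% | 80.4% | 5.0% |
| 2.5 | 66.0% | 65.0% | 7.6% |
| 5 | 47.5% | 46.7% | 15.8% |
| 7.5 | 29.6% | 29.1% | 29.6% |
| 10 | 15.6% | 15.5% | 47.5% |

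With b above zero, most of the rejections in the last column favour control; at 5 mm it is 15.6 of the 15.8 percentage points. A shift of 5 mm is one third of the 15 mm target and one fifth of the SD.

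**The case against.** The case for the plan has real substance.

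- **The nurse is present in both arms.** A reader might infer that courtesy acts in the control arm only. The text does not support that: the nurse applies the intervention and takes the ratings in both groups, and the Discussion's remark about socially acceptable answers is not limited to one arm. Only the between-arm difference in courtesy matters. This stands, and it is why the shift above is a net one.
- **The protocol states a risk.** A reader might infer that bias is established. It is not; its size is unknown and the table is illustrative.
- **Satisfaction with a person is part of the comparator.** Some uplift from personal contact is true satisfaction with the control. This stands too. The concern covers only the part that arises because the rated person collects the rating.
- **Handling may be covered elsewhere.** To administer a scale need not mean watching it being marked, and a standard operating procedure exists. That is fair, but the Discussion, where the authors answer this very risk, does not mention private completion.
- **The quiz.** A reader might infer that the post-intervention quiz is also biased towards control. No passage gives a direction for it. The child completes it, and the change from researcher at baseline to nurse afterwards is the same in both arms.
- **Allocation.** A reader might infer a concealment failure because the treating nurses allocate. Consent and baseline measures are completed by the blinded researcher before allocation, so this point does not show one.

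**Conclusion.** The concern holds for the satisfaction VAS. An unblinded nurse, who in the control arm is rated on her or his own advice, administers the outcome that determined the sample size. The protocol names the risk and its direction, and deserves credit for doing so, but its safeguards leave the t test unprotected. The exact statement is that courtesy is likely to be unequal and to favour control, by an unknown amount.

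The figures of about 16% false rejection and about 47% power rest on an assumed net 5 mm shift, the protocol's SD of 25 mm, 45 analysed per arm and a two-sided 5% test. They show that a modest shift would matter. They do not show that it occurs. The case for change rests on an acknowledged bias that can be reduced at very little cost, not on a demonstrated distortion.

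**What to change.** Amend the Procedure for recruitment and application of intervention so that, in both arms:

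1. The parent and child mark the VAS privately, with the nurse out of the room.
2. The form goes into a sealed envelope carrying only the study number, opened by someone other than the treating nurse.
3. The date of the change is recorded, because Trial status says recruitment is under way, and VAS results are reported before and after that date.

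In Randomization and blinding, state that blinding covers the researcher and the statistician but not the collection of the VAS or the immediate quiz.

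The blinded researcher should not be brought back to take these measures. Children aged four to ten could easily reveal which session they had, and his blinding would be put at risk.

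The cost is envelopes and one line in the operating procedure, with no change to staff or sample size. There are two small downsides: parents rather than the nurse will help young children mark the scale, and the VAS data will have been collected in two ways.

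### The researcher declared blind through data entry collects diary booklets whose inner page identifies the arm

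*Protocol article*

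**What the plan says.** Under Randomization and blinding, the researcher who recruits and collects data "will remain blinded all through data collection and input". Only when data collection is over does a second, unblinded researcher "break the randomization code to input the group allocation within the pre-existing data set", and the statistician is to stay blinded during the analysis.

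Procedure for recruitment and application of intervention has the first researcher leave before the nurse allocates the family, expressly to protect his blinding. The nurse then hands out a booklet holding a toothbrushing diary and a snack diary. In the game arm, "The booklet given to children from the study group will also contain a page in which they can write five ‘secret words", words that appear only in the DVD version of the game. "Children from the control group will have a simple colouring page instead". The blinded researcher is to "go to the day surgery unit on the day of the child’s general anaesthesia procedure to collect the booklet". He later telephones the parents at three months to offer a review visit.

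Under Outcome measures, diary return is among the primary outcomes. Secret-words completion (game arm only), verbal feedback and review attendance are secondary. Under Statistical analysis, the toothbrushing and snack scores are compared between arms by t test.

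**The concern.** The procedure protects the blind at allocation and then exposes it at collection. A page that exists in one arm only is bound into the instrument that the blinded researcher collects and that must be opened to score the diaries. The statement of blinding covers data entry explicitly, so this is a conflict between two sections of the same article and not a detail left to a fuller document.

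Two things are at stake. The first is observer bias in diary scoring and in any later contact with the family. The Discussion itself warns that families may record the expected answer in diaries and that parents may give socially acceptable replies, and outcomes of this kind benefit most from a blinded handler. The second is interpretation: the object whose return is counted as a primary outcome carries a different task in each arm.

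**Working it through.** No figure in the plan is in dispute, so the check sets the sections side by side in time order.

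1. **Pre-assessment clinic, about two weeks before surgery (Methods and design).** The researcher takes the baseline measures and leaves. The nurse allocates, intervenes, and collects the second quiz, both satisfaction scales and the verbatim feedback. The researcher is blind, and nothing here depends on the booklet.
2. **Day of surgery.** The researcher collects the booklet. The article describes a difference on an inner page and does not say that the covers differ, so receiving a closed booklet need not unblind him.
3. **Opening and data entry.** The diaries and the arm-specific page are in the same booklet. Whoever scores the diaries can see the page, and a page of secret words or a colouring page identifies the arm. The article mentions no seal, separate handler or removal of the page. The prepaid-envelope route in the Discussion names no other recipient; a mailed booklet only arrives later.
4. **Three-month call.** This is made by the same researcher, after step 3. Review attendance is an outcome, and his call is the means by which the review is offered.
5. **Three-month quiz and dietary questionnaire.** Both are primary outcomes. The child and the parent complete them; the article does not say who administers them.
6. **Data set.** Allocation is meant to be added only after collection ends. Secret-words completion can have a value only in the game arm, and verbatim feedback will often name the intervention. If either is in the file before the code is broken, allocation can be read from it.

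Exposure by outcome:

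| Outcome | Exposed to this breach? |
|---|---|
| Satisfaction scale; immediate quiz | No |
| Toothbrushing and snack diary scores | Yes, at scoring only; the child has already filled them in |
| Diary return | Instrument differs by arm; direction unknown |
| Review attendance | Yes, through the call |
| Three-month quiz and dietary questionnaire | Only if the researcher administers them |
| Statistician's blind | Only if secret words or feedback enter the file |

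**Illustration of size.** The documents give no observer effect, so I assume a spurious shift d of 0.1 to 0.2 SD across a whole comparison. With 108 recruited and 20 % lost, 108 × 0.80 / 2 ≈ 43 remain per arm. The noncentrality is d × √(n/2): 0.1 × √21.5 = 0.46 and 0.2 × √21.5 = 0.93. A two-sided 5 % t test then rejects in 7.4 % and 15.0 % of trials with no true effect. At the planned 45 per arm the rates are 7.6 % and 15.5 %. Unreturned booklets unblind nobody, so incomplete return would lower these rates.

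**The case against.** The strongest defence is that the exposure is narrow. Sample size rests on satisfaction, which the nurse collects before any booklet comes back. The diaries are completed before the researcher could see the page, so he cannot prompt their content. The three-month instruments are completed by parent and child, which limits an assessor's discretion. All of this stands, and it lowers the severity.

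It can also be said that someone else may open the booklets under a safeguard in the full protocol or the missing figures. That is possible. But the article names this researcher as collector and declares him blind through data entry, and nothing in it reconciles the two.

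Four stronger readings are tempting and are not supported:

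- A reader might infer that the booklets look different from outside. The text describes only an inner page.
- A reader might infer that an unblinded researcher takes all the three-month measures. Only the call is attributed to him.
- A reader might call diary return confounded. The arms are randomized and the DVD is part of the game package, so a difference in return is an effect of the assigned package. What is lost is attribution to the education alone. Prizes, reminders and prepaid envelopes are described without distinction by arm, and the colouring page balances the booklets in part.
- A reader might conclude that the statistician is unblinded. This depends on what enters the data set, which the article does not say. No between-arm test of secret words is planned.

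**Conclusion.** The point holds as a conflict between the two sections: the stated blinding of the researcher cannot be relied on once booklets are opened or their data entered. That is usually from about two weeks after the intervention and before the three-month call.

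Diary scoring and review attendance are exposed under the procedure as written, on the natural reading that the researcher who collects the booklets also sees their contents. The three-month quiz and dietary questionnaire, and the statistician's blind, are exposed only under the conditions given above. Separately, a difference in diary return cannot be attributed to the education alone, and its direction cannot be predicted.

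The amount of bias is unknown; the rejection rates above rest wholly on an assumed shift and only show scale. Since the outcome that sizes the trial is unaffected, this should be fixed but does not undermine the trial's main comparison.

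**What to change.** Use the same diary booklet in both arms. Put the secret-words page or the colouring page on a separate sheet, returned in a sealed envelope addressed to the unblinded researcher already in post. That researcher alone should enter the sheet and the verbatim feedback, and merge them only after the between-arm analysis file is locked. The protocol should also state who administers the three-month measures and whether that person is unaware of allocation.

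The cost is a reprint and one envelope per child, with no extra staff. Trial status says that recruitment began in October 2013, so a change now creates two booklet versions behind a primary outcome; record which version each child received.

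For booklets already returned, or if the booklet cannot be changed, withdraw the statement that the researcher is blinded after booklet collection, and report the diary and three-month outcomes as not reliably assessor-blinded. In either case, report diary return as an effect of the whole package, booklet task included.
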